### Study evaluation

A logic model for evaluation of this study is presented in figure 2. The model summarises the activities involved in the development and implementation phases, as well as the projected outcomes. The model will be used to frame our approach to evaluating (1) whether the trial was developed and implemented as intended (fidelity and reach), (2) whether study outcomes were achieved or not, (3) the influence of situational factors on results obtained. Baseline surveys, results from the screening and QUM services and pharmacists’ interviews will be used to assess these activities.

**Figure 2 F2:**
[figure not shown]
Pharmacy based screening and QUM study logic model. CKD, chronic kidney disease; CPD, Continuing Professional Development; cRCT, cluster randomised controlled trial; CrCL, creatinine clearance; eGFR; estimated glomerular filtration rate; GP, general practitioner; POCT, Point-of-Care Testing; QUM, quality use of medicines; SCr, serum creatinine.

### Baseline evaluation

At the beginning of the study, participating pharmacies will be required to complete a baseline survey that includes questions on pharmacy characteristics, existing professional services (remunerated and non-remunerated) and strategies and capacity for implementing these services. The information collected will be used to inform the comparability of the two arms in the trial and health economic analysis. All data entered by participant pharmacists into the study software will be extracted to generate quantitative data to enable the trial process evaluation.

### Impact evaluation

The impact of the screening and QUM services will be determined by testing the clinical hypothesis as detailed in the clinical protocol and outcomes sections.

### Midtrial interviews

Three months after the implementation of the service in the pharmacy, a mix of pharmacists from high and low performance groups in both arms will be invited to participate in an interview to provide feedback to identify challenges, opportunities, barriers and facilitators to service implementation. This will enable us to provide support to pharmacies and adapt where appropriate.

### End-of-trial interviews

At the end of the study, pharmacists from participating pharmacies representing a mixture of both high recruitment and low recruitment, will be interviewed to gain feedback on the service implementation in the pharmacy, identifying barriers and facilitators to implementing the trial in the pharmacy, perceptions of sustainability and level of engagement by the local GPs in the referral process.

All study participants will receive a survey to determine their quality of life and well-being. Referred participants will also receive a survey to determine their level of satisfaction and willingness to pay for the provided service. A random sample of 20% non-referred participants will be surveyed to determine their overall experience and level of satisfaction with the service. A random sample of 10% of GPs who had patients referred to them during the trial will be invited to respond to a telephone/electronic questionnaire to determine their overall experience and level of satisfaction with the service.

All surveys will be created on Research Electronic Data Capture, a secure web-based application designed to support data capture for research studies hosted at The University of Sydney.^43^ Qualitative interviews will comprise open-ended questions that prompt discussion on a wide range of topics including overall experience with the study, consumer feedback, interaction with GPs and impact of the trial in their pharmacy.

### Economic evaluation

Health service utilisation will be measured through Medicare and Pharmaceutical Benefits Schemes (MBS and PBS) data linkage, to quantify the symptom-specific and total health service resource use and costs at 12 months, by allocated group. The Consolidated Health Economic Evaluation Reporting Standards guidelines (online supplemental appendix 3) will be followed when reporting the health economic evaluation.^44^

10.1136/bmjopen-2023-079110.supp3Supplementary data

### Costs

Cost-effectiveness of the intervention will be calculated from a health service provider perspective considering costs incurred by the pharmacists and the government (PBS/MBS) but will not include costs borne by screening participants (eg, through co-payments charged by GPs). Healthcare resource use including GP visits, specialist visits, diagnostic tests, medicine, hospitalisation, emergency admissions will be collected from MBS/PBS history, medication prescription and dispensing records and previous hospital discharge summaries from My Health Record. Unit costs will be collected based on MBS/PBS item numbers, Australian Refined Diagnosis Related Groups and Triage codes. Measured costs will include pharmacist time to facilitate data collection at each pharmacy.

#### Costs analysis

The cost per new CKD case diagnosis for each group will be estimated and compared. We will assess whether the average cost of the new CKD case diagnosis in the intervention group is lower or higher than the average cost of the new CKD case diagnosis in the control group. We hypothesise that there is likely to be a difference in average costs per new CKD case diagnosis across the sites in the same cluster and across the clusters from the metropolitan and rural settings. This is due to the differences in sample size, local unit prices of equipment, staff costs and different established local practices.

Differences in overall mean costs between the two groups will be analysed using Generalised Linear Mixed Model. The distribution of residuals from the regression model will be examined and a decision will be made as to whether the costs should be logarithm transformed. Any extreme costs will be carefully examined to decide if they should be considered as extreme outliers and should be trimmed (removed) from the analysis. It is anticipated there will be some missing data. Missing costs data will be examined to ascertain whether it is missing completely at random, missing at random or missing not at random. Simple and multiple imputation methods will be considered based on the pattern of missingness.^45^

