#### Modelled cost-effectiveness analysis

The modelled economic evaluation would investigate the benefits of early diagnosis of CKD cases and the associated prevention/delay of the CKD complications like use of kidney replacement therapies or mortality in the long term. The modelled economic evaluation will include the long-term costs of treatment, regular laboratory investigations, treatment of adverse events, hospital admissions and other relevant costs.

The long-term improved outcomes are hypothesised to translate into a cost reduction and offset the increased costs associated with adding pharmacy-led screening to no screening, for CKD case diagnosis. The modelled economic evaluation will also use published results of long-term observational studies to derive assumptions for the decision analytical modelling and to populate the model. A 5% discount rate will be applied to both costs and benefits.^46^ The uncertainty about results of economic evaluation will be explored using a non-parametric bootstrapping method.

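### The cost analysis leaves open removing or log-transforming high costs after inspection, which would abandon the mean cost difference, and it compares average rather than incremental cost per new CKD diagnosis.

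*Protocol article*

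**What the plan says.** The Costs analysis section sets the target: "Differences in overall mean costs between the two groups will be analysed using Generalised Linear Mixed Model". Two data-dependent choices follow. After the residuals are examined, "a decision will be made as to whether the costs should be logarithm transformed". And high costs are to be inspected to judge whether they count as "extreme outliers and should be trimmed (removed) from the analysis". The article gives no threshold, does not limit removal to data errors, and mentions neither an untrimmed main analysis nor a return to the original scale after a log model.

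The same section treats detection costs separately: "The cost per new CKD case diagnosis for each group will be estimated and compared". The criterion is whether the "average cost of the new CKD case diagnosis in the intervention group is lower or higher than the average cost" in the control group.

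Three other sections bear on this. Costs counts hospital and emergency admissions among the resources to be costed. Within-trial cost-effectiveness analysis plans an incremental ratio of intervention to control, per QALY only. Modelled cost-effectiveness analysis plans a non-parametric bootstrap and speaks of "the increased costs associated with adding pharmacy-led screening to no screening, for CKD case diagnosis".

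**The concern.** An incremental cost-effectiveness ratio needs the difference in arithmetic mean cost per participant. Removing true high costs takes away part of each arm's mean. A log model without retransformation compares geometric means. Neither gives that difference.

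The upper tail matters in this trial. Admissions are likely to be the largest single costs. Medication-related hospitalisations are a secondary outcome, and the Discussion hopes the service will reduce them. The costs most exposed to trimming are therefore those through which the intervention might save money. A rule settled only after the costs have been seen can move the result in either direction.

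The cost-per-diagnosis comparison has a different weakness. Participants in the control arm can be diagnosed too, so a decision-maker needs the extra cost of each extra diagnosis. Two within-arm averages do not give that figure, and the intervention's average can be the lower one even when every additional case is bought at real cost.

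**Working it through.** **Inputs.** The article gives no cost, cost SD or target ratio, so there is no cost figure of its own to reproduce. From the Sample size section: 10% diagnosed under control and 15% under intervention (the 5-point increase used for the design). These rates do underlie the stated design: two proportions at 80% power need 686 per arm; the design effect is 1 + 29 × 0.05 = 2.45; 686 × 2.45 / 30 = 56.02, which rounds up to the stated 57 clusters. All costs, spreads and admission rates below are assumptions, in arbitrary currency units.

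**1. Trimming.** Assumed mean cost without admission is 1000 (control) and 1150 (intervention), and mean admission cost is 15000, all gamma-distributed. Two million participants per arm were simulated, and costs above a pooled percentile were removed.

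- Admissions 5% and 3%: expected means are 1000 + 0.05 × 15000 = 1750 and 1150 + 0.03 × 15000 = 1600, a difference of -150.
- Admissions 3% in both arms: 1000 + 450 = 1450 and 1150 + 450 = 1600, a difference of +150.

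| Intervention minus control | Untrimmed | Top 1% removed | Top 2.5% removed | Top 5% removed |
|---|---|---|---|---|
| Admissions 5% and 3% | -153 | -6 | +101 | +121 |
| Admissions 3% and 3% | +151 | +147 | +148 | +111 |

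In the first row the saving comes from avoided admissions. Trimming removes it and the sign reverses. In the second row there is no such saving to remove, and the change is small until the trim exceeds the 3% who were admitted and cuts into ordinary costs.

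**2. Log transformation.** For lognormal costs, the arithmetic mean is the geometric mean × exp(s²/2), where s is the SD of log cost. Take a geometric mean of 1000 in both arms with s = 1.0 and 1.2:

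- 1000 × exp(0.50) = 1649
- 1000 × exp(0.72) = 2054
- difference about 406, while the ratio of geometric means is 1.00

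In the 5% and 3% admission scenario above, the geometric mean ratio is 1.08, pointing to higher intervention cost although the mean difference is -153.

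**3. Average and incremental cost per diagnosis.** The average in an arm is C/p. The incremental cost is (C1 - C0)/(p1 - p0). With p0 = 0.10, p1 = 0.15 and C0 = 1000:

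| C1 | Control average | Intervention average | Per extra diagnosis |
|---|---|---|---|
| 1100 | 10000 | 7333 | 100/0.05 = 2000 |
| 1300 | 10000 | 8667 | 300/0.05 = 6000 |
| 1500 | 10000 | 10000 | 500/0.05 = 10000 |
| 1600 | 10000 | 10667 | 600/0.05 = 12000 |

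At these rates the intervention's average is lower whenever its cost per person is less than 0.15/0.10 = 1.5 times the control cost. That comparison does not show what an additional case costs.

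**The case against.** The strongest reply is that the right quantities are already planned: a difference in mean costs, an incremental cost per QALY and a bootstrap. Trimming and transformation are only possibilities, and a condensed article may leave thresholds and retransformation to a fuller plan. This stands in part. A reader might infer that the trial will fail to estimate its incremental cost; the text does not support that, because neither step is committed to and the QALY ratio is not tied to trimmed or logged costs. Equally, nothing ties that ratio to complete costs. The article itself names removal as an option for the analysis, so the point concerns what is stated, not an omitted detail.

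It is also fair that the effect may be small. With equal admissions, a 1% or 2.5% trim changes little. If log-variances are equal, the ratio of geometric means equals the ratio of arithmetic means, although it is still a ratio and not the difference required.

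On cost per diagnosis, the comparison is openly one of averages, and the incremental figure could be computed from planned results. Its absence biases no planned estimate. The weakness is the lower-or-higher criterion, which can be misread as showing value for money.

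Two further inferences go too far. One is that whoever removes costs will know the allocation; the article is silent on this. The other is that the no-screening phrase fixes the long-term model's comparator. It occurs in a sentence about hoped-for cost offsets, and a model may legitimately include a no-service scenario. It is a wording mismatch with a control arm that receives QKidney risk assessment.

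**Conclusion.** The point holds in conditional form. If trimming or an unretransformed log model is used in the main analysis, the result is no longer the arithmetic mean cost difference, and genuine admission costs may be lost. The effect ranges from small to a change of sign, depending on whether admissions differ between arms; those sizes rest wholly on assumed costs and admission rates. Separately, comparing averages does not give the cost of an additional diagnosis. That follows from the definitions, and only its size depends on the assumed costs. Cost-effectiveness is one of several secondary outcomes, so neither primary conclusion is affected. The change is still worth making before any cost data are inspected.

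**What to change.** - Keep all verified costs in the main analysis and correct only demonstrable data errors.
- Estimate the arithmetic mean cost difference on the original scale, for example with a gamma-family model within the planned mixed-model framework, allowing for clustering. State that the cost-per-QALY ratio uses these costs.
- Present trimming only as a sensitivity analysis, with its threshold fixed in advance.
- Replace or supplement the comparison of averages with incremental cost per additional CKD diagnosis, with uncertainty from a bootstrap that resamples whole clusters.
- Reconcile the no-screening wording under Modelled cost-effectiveness analysis with the trial's QKidney control, and label any no-screening comparison as a modelled scenario.

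This changes only the wording of the economic analysis and needs no new data. The price is wider intervals for mean cost differences, because the high costs stay in.

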### Effectiveness

Based on the EQ-5D-5L, utility weight will be calculated via an Australian algorithm, which will be used to obtain quality adjusted life-years (QALY).

#### Within-trial cost-effectiveness analysis

Incremental cost effectiveness ratios that allow analysis of incremental costs of intervention group versus control group per one QALY gained will be calculated.

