### Hypotheses

We hypothesise that the use of a POCT with CKD risk assessment (POCT+QKidney Risk Assessment: Intervention Group) in community pharmacies will result in (1) a significantly improved detection of previously unknown CKD cases, and (2) reduced use of potentially inappropriate medications when compared with CKD risk assessment alone (QKidney Risk Assessment: Control Group).

Other hypotheses related to the primary hypothesis are that the Intervention Group will be associated with a statistically significant increase in the proportions of those who are referred to the GP, take up referral with the GP, are newly diagnosed with CKD compared with the Control Group.

Additionally, the incorporation of POCT in conjunction with the QKidney Risk Assessment will lead to enhanced utilisation of kidney beneficial medications (ie, those that slow kidney disease progression), a long-term economic benefit and improved humanistic outcomes.

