#### Sample size

Sample size selection and estimation was performed based on the CKD diagnosis. Using the GRT sample size calculator,^35^ it is estimated that the intervention will increase diagnosis from the current CKD prevalence of 10% to between 15% and 20%, an increase of 5%–10%. Sample size is estimated based on a 5% increase in diagnosis of CKD. With 80% power, alpha of 0.05 and intraclass correlation coefficient (ICC)=0.05, at least 57 clusters are required per arm. Based on our sampling model, cluster size has been increased to 61 per arm to account for attrition. With an average number of 30 participants per cluster, the total sample size to be targeted is 3660. Based on previous study^11^ that showed a reduction of inappropriate medications in CKD from 32.3% to 17.5% (an approximate reduction of 15%), with 90% power, alpha=0.05 and ICC of 0.05 and a cluster size of 30 per cluster, 19 clusters in each arm are required (38 clusters in all) with a sample size of 1140 for the other primary outcome, that is, change in inappropriate medication use. The sample size required for the diagnosis outcome is, therefore, sufficient to cover the sample size required for the medication changes outcome.

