#### Secondary outcome measures

Proportion of screening participants with inappropriate medications (number of medications at inappropriate high dose based on the kidney function and number of contraindicated medications).Proportion of eligible participants without potentially beneficial medications (eg, renin angiotensin system inhibitors or sodium glucose co-transporter 2 inhibitors).The number and characteristics of proposed medication adjustments recommended by pharmacists and acceptance rates by GPs.Proportion of participants with CKD risk factors.Proportion of participants screened (process indicator).Participants’ QKidney risk profiles.Percentage of participants referred to their GP.Percentage of participants who take up referral with their GP.Number of hospitalisations due to medication-related events.Cost effectiveness.Health-related quality of life, consumer well-being and satisfaction.

Both the intervention and control group participants will be followed-up by the project officers/pharmacists at 6 and 12 months to determine if they have had any additional blood tests, and changes to their medications, and hospitalisations.

Primary outcomes will be determined based on data collected from GPs. Health-related quality of life and overall participant well-being will be measured using the EuroQoL-5D-5L, which consists of a descriptive system and a Visual Analogue Scale.^39^ The EQ-5D-5L is scored on a 0–1 utility scale, where 0=death and 1=full and complete health. Unit values will be informed by Australian population estimates.^40^ A minimally important difference of 0.07 (7%) change in utility on the EQ-5D-5L scale is considered to be clinically meaningful.^41^

Screening participants’ satisfaction with the service and willingness to pay for the service will be determined by a telephone questionnaire, which will include items relating to service approval (5-point Likert scale); and open-ended questions to elicit reasons for approval and satisfaction ratings. Screening participants’ willingness to pay for the service will also be determined including the maximum amount. Satisfaction of pharmacists (at midtrial and end of trial) with the screening and QUM services will be assessed using electronic surveys. The GPs involved in the care of the participants will also be sent a survey at the end of the trial to determine their satisfaction and any effects on their practice.

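### The within-trial QALY result is a 12-month cost-per-QALY ratio that may have an unstable sign, with no net-benefit measure and no resampling unit stated for the bootstrap

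*Protocol article*

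**What the plan says.** The section on within-trial cost-effectiveness contains one statement: "Incremental cost effectiveness ratios that allow analysis of incremental costs of intervention group versus control group per one QALY gained will be calculated". The 12-month horizon comes from elsewhere. The Economic evaluation section refers to "total health service resource use and costs at 12 months, by allocated group", and Table 1 marks health-related quality of life at baseline and 12 months only. On the source of QALYs, the Effectiveness section says "Based on the EQ-5D-5L, utility weight will be calculated via an Australian algorithm".

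Uncertainty is covered by one sentence, placed at the end of the section on modelled cost-effectiveness: "The uncertainty about results of economic evaluation will be explored using a non-parametric bootstrapping method". It does not say what is resampled or how the replicates will be presented.

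Other within-trial economic results are planned. The Costs analysis section says "The cost per new CKD case diagnosis for each group will be estimated and compared", and it analyses the difference in mean costs with a generalised linear mixed model. The Data analysis plan applies generalised estimating equations, clustered by pharmacy, to all primary and secondary analyses, and cost effectiveness is listed among the secondary outcomes. The adjusted analyses use age, gender, blood pressure, BMI, socioeconomic status and pharmacy location. Baseline EQ-5D utility is not in that list.

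No size is given for the expected QALY difference. The Hypotheses section expects "a long-term economic benefit and improved humanistic outcomes", and the outcomes section says "A minimally important difference of 0.07 (7%) change in utility on the EQ-5D-5L scale is considered to be clinically meaningful".

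**The concern.** A ratio is readable only when its denominator is clearly of one sign. Otherwise a negative ratio can mean cheaper and better or dearer and worse, and a positive ratio can mean dearer and better or cheaper and worse. These are opposite conclusions under one sign, so neither the ratio alone nor an ordering of bootstrap ratios can be interpreted safely.

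The article's own framing makes a small 12-month QALY difference plausible. The economic benefit is described as long term, and the model is there to capture delayed complications, kidney replacement therapy and mortality. The effect for which the trial is sized is a modest rise in diagnoses.

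The bootstrap raises a second issue. Participants in one pharmacy are correlated, and resampling them as if independent understates uncertainty. The article leaves the unit open, and its use of the word cluster does not settle it. The design overview calls pharmacies the clusters and the unit of randomisation, but it also describes clusters as groups of co-located pharmacies, allocated in matched pairs.

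At stake is whether the within-trial economic result can be read at all, and how wide its stated uncertainty is. The primary outcomes are not affected.

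**Working it through.** **Inputs from the article.** Diagnosis 10% to 15%, 80% power, two-sided alpha 0.05, ICC 0.05, 30 participants per cluster, 57 clusters per arm raised to 61, total 3,660 (Sample size); meaningful utility change 0.07 (Secondary outcome measures); EQ-5D-5L at baseline and 12 months (Table 1).

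**Assumptions (not in the article).** Utility SD 0.15 to 0.25, correlation 0.6 between baseline and 12 months, ICC for utility or QALYs 0.01 to 0.05, linear change over the year, no loss to follow-up. The 0.05 is the article's ICC for diagnosis, borrowed here.

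**1. The plan's own figure.** Two proportions, 0.10 versus 0.15, need 686 per arm. The design effect is 1 + 29 × 0.05 = 2.45, and 686 × 2.45 / 30 = 56.02, so 57 clusters per arm. Also 61 × 2 × 30 = 3,660, or 1,830 per arm. Both agree with the article. It gives no figure for the QALY difference.

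**2. QALY difference if only the extra diagnosed benefit.** The mean utility gain at 12 months is 0.05 × 0.07 = 0.0035. With a linear rise, the area under the curve is 0.0035 / 2 = 0.00175 QALY.

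**3. Standard error, adjusted for baseline utility.** SE = ½ × SD × √(1 − 0.6²) × √(2 × DE / 1,830), with DE = 1 + 29 × ICC.

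| Utility SD | ICC | SE (QALY) | 0.00175 / SE | P(wrong sign) |
|---|---|---|---|---|
| 0.15 | 0.01 | 0.0023 | 0.78 | 22% |
| 0.20 | 0.05 | 0.0041 | 0.42 | 34% |
| 0.25 | 0.05 | 0.0052 | 0.34 | 37% |

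The last column is Φ(−0.00175 / SE).

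**4. Larger effects, without baseline adjustment.** Here the QALY SD is assumed to be 0.10 to 0.20 and the ICC 0 to 0.05, so SE = SD × √(2 × DE / 1,830) = 0.0033 to 0.0103.

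| Who gains | Mean QALY gain | P(wrong sign) |
|---|---|---|
| Extra 5% gain 0.07 | 0.00175 | 30% to 43% |
| Extra 10% gain 0.07 | 0.0035 | 14% to 37% |
| 20% of participants gain 0.07 | 0.007 | 2% to 25% |
| Average participant gains 0.035 | 0.0175 | under 0.1% to 4.5% |
| Average participant gains 0.07 | 0.035 | at most 0.04% |

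**5. Value of the baseline measurement.** With equal SDs at both times and correlation 0.6, the unadjusted QALY SD is SD × √((1 + 0.6) / 2) = 0.894 × SD. After adjustment it is ½ × 0.8 × SD = 0.4 × SD. The unadjusted standard error is therefore larger by 0.894 / 0.4 = 2.2. The figures in step 3 already take credit for this adjustment, which the listed covariates do not include.

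**6. If individuals were resampled.** The standard error would be too small by √DE, and a nominal 95% interval for the QALY difference would cover 2Φ(1.96 / √DE) − 1.

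- ICC 0.01: √1.29 = 1.14, coverage about 92%.
- ICC 0.05: √2.45 = 1.57, coverage about 79%.

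A simulation with 61 clusters of 30 per arm and QALY SD 0.15 gave about 91% and 77% to 80% for individual resampling, against 93% to 96% for whole-cluster resampling.

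**The case against.** The strongest reply is that most of this depends on facts that the article does not state. It gives no expected QALY difference, utility SD, baseline correlation or utility ICC, and it hypothesises improvement. The medication service also reaches people with known CKD and those at moderate to high risk, so benefit need not be confined to new diagnoses. The 0.07 is a threshold for a meaningful change, not a forecast gain per diagnosis. This stands: the unstable sign is a plausible scenario, and it disappears if the average participant gains about 0.035 or more.

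A reader might infer that the bootstrap ignores clustering. The documents do not support that. The resampling unit is unstated, and the article recognises clustering in its estimating equations and plans a mixed model for costs. An article may also leave this detail to a fuller plan.

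A reader might infer that an invalid confidence interval for the ratio is planned. None is promised, and bootstrap replicates could equally feed a cost-effectiveness plane or an acceptability curve.

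A reader might infer that the ratio is the only within-trial economic result, or that the trial could not judge whether the service is worth its cost. Neither follows. Cost per diagnosis and the difference in mean costs are also planned, quality of life is analysed separately, and the long-term question is given to the model.

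What survives is that the only named within-trial QALY result is a ratio that may be hard to read, with no stated measure that avoids the difficulty. Cost per new diagnosis compares each arm's average and does not give the incremental value of the service.

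**Conclusion.** The point holds in a conditional form. On the trial's design effect ("Sample size is estimated based on a 5% increase in diagnosis of CKD", taken as 5 percentage points) and a gain of 0.07 in each extra person diagnosed, the mean gain is about 0.00175 QALY against a standard error of 0.0023 to 0.0052. The sign would then be wrong in about 22% to 37% of trials. This rests on the assumed SD, correlation and ICC, and on benefit being confined to the extra diagnosed. With an average gain of 0.035 or more, the chance is at most about 4.5%, the upper end being for an unadjusted QALY SD of 0.20 and ICC 0.05.

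The bootstrap is underspecified; it is not shown to be wrong. The cost of choosing individual resampling would be a standard error too small by a factor of 1.14 to 1.57, depending on an assumed ICC. Leaving out baseline utility, which is collected, would give up precision for no saving.

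Priority is modest. This is a secondary outcome, and the main economic question is left to the long-term model.

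**What to change.** In the section on within-trial cost-effectiveness:

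- Report incremental net monetary benefit at stated willingness-to-pay values, with an acceptability curve, beside the cost-per-QALY ratio. Show the separate cost and QALY differences with the ratio.
- Adjust the QALY difference for baseline EQ-5D utility within the clustered model.
- State that the bootstrap resamples whole randomised clusters within arm, keeping each participant's cost and QALY together. Say whether the randomised cluster is the single pharmacy or the group of co-located pharmacies.

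The cost is some wording and slightly more analysis. No new data are needed. The stated uncertainty may become wider than under individual resampling.
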